## Statistical methods

### Sample size calculation

Assuming that the average score of the primary outcome measure (ICIQ-UI-SF; range 0–21) of MOTHERFIT1 will lie at 8 and for MOTHERFIT2 at 9 (which is also the expected mean ICIQ-UI-SF score at 18 months post-partum in the CAU group; in contrast, the expected mean ICIQ-UI-SF score at 18 months post-partum in the experimental group is 5 (for MOTHERFIT1 and MOTHERFIT2) together with a relatively high standard deviation of 5 at baseline (because of the non-normality of the measure), participants will – with 97.5% probability – vary at baseline within the ranges of 0 to 19. The minimum acceptable score of participants to be treated is set at 3, so the range lies approximately between 3 and 19. From earlier studies [44], it became clear that the success of the PFMT exercises will be considerable and will be clinically relevant if the gain is higher than half the standard deviation of the baseline, presumably 3 with a somewhat smaller standard deviation of 3, because of the homogenising effects in the experimental arm. In contrast to MOTHERFIT1 (women remain stable), in MOTHERFIT2 it is assumed that the condition of CAU participants at 18 months will worsen with an average ICIQ-UI-SF score going from 9 in the baseline to 10 (SD 5).

Assuming two-sided testing, a power of 90% (beta = 0.10) and a significance level of 0.95 (alpha = 0.05) in each arm of the trial in MOTHERFIT1, minimally 60, and in MOTHERFIT2, minimally 35 participants will have to be included without taking into account that participants may drop out of the study during the 18 months of observations. Using a 20% dropout, in MOTHERFIT1 each arm will need 75 participants, 150 in total, and in MOTHERFIT2 each arm will need 45 participants, 90 in total.

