### Descriptive analysis

Firstly, descriptive, univariate statistics will be reported. In case of metric, normally distributed variables, mean and standard deviations are presented. If not normally distributed, medians and percentiles are presented. The Shapiro-Wilk test will be used to assess normality.

Process and structure indicators will be analysed with descriptive statistics and presented as absolute and proportion data (%) whenever the variable is categorical, or as mean (± standard deviation; 95% confidence intervals) or quartiles for continuous variables. A *p* value < 0.05 will be considered to be statistically significant. Data analysis will be carried out using SPSS version 25 (IBM. Corporation, Somers. NY, USA).

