### Analysis of main hypotheses

In both studies, the main hypothesis concerns differential changes in ICIQ-UI-SF within time between two randomised groups of participants. (Repeated measurements) analysis of covariance (ANCOVA) will be performed with baseline measurements (T0) as covariate. Transformations of original scores will be attempted if the ICIQ-UI-SF shows a non-normal distribution at T0. Randomisation groups (motherfit group therapy versus CAU) are regarded as a between factor. Next, the within-participants linear trend in time of the outcome will be calculated with the weights from the first orthogonal polynomial contrast and this is used as a dependent variable in a multiple (dummy-)regression analysis. It concerns repeated measurements from T0 to T4 (MOTHERFIT1) and T0 to T3 (MOTHERFIT2). Next to the baseline covariate measurement and the randomisation groups’ dummy variable, other possible confounding variables will be used in this multiple linear regression analysis of the linear trend in time of the ICIQ-UI-SF.

The following potential confounding variables are considered to be used in the multiple linear regression analysis: Body Mass Index (BMI) before pregnancy (> 25), parity, maternal age (> 35 years) and the ability to perform a PFM contraction at baseline.

Forward selection and backward elimination techniques will be used to determine the best fit of the data to a final regression model. Testing of interactive relationships between statistically significant effects of predictors in the final model will be done, especially if it concerns the experimental between-randomisation groups’ factor. Listwise deletion of missing cases will be used in all linear regression modelling. This may be in case of loss-to-follow-up because of a succeeding pregnancy during the follow-up period of 18 months. For the final best-fitting regression model, a residual analysis will be done on the standardised Studentised z-scores and a screening will be performed on outliers to ensure the legitimacy and validity of the use of parametric statistics in analysis by testing the normality of distribution of the linear trend in ICIQ-UI-SF.

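### Forward/backward selection picks the final regression for the main hypothesis without protecting the group and T0 terms, and score transformation is tied to normality of T0

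*Protocol article*

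**What the plan says.** The section Analysis of main hypotheses sets out a sequence that applies to both trials.

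- First comes a (repeated-measures) ANCOVA with T0 as covariate and randomised group as the between factor.
- Each woman's linear trend over time is then regressed on T0, the group dummy and possible confounders. The candidates are pre-pregnancy BMI above 25, parity, maternal age above 35, and ability to contract the pelvic floor at baseline.
- For that regression, "Forward selection and backward elimination techniques will be used to determine the best fit of the data to a final regression model". No term is declared exempt.
- After selection, "Testing of interactive relationships between statistically significant effects of predictors in the final model will be done", with particular attention to the randomised-group factor.
- On scale, "Transformations of original scores will be attempted if the ICIQ-UI-SF shows a non-normal distribution at T0". No transformation is named. The Descriptive analysis section adds that "The Shapiro-Wilk test will be used to assess normality".

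The same handling is extended to IIQ-7, GPE and EQ-5D-5L. Under Participants, entry requires an ICIQ-UI-SF score above 3. Under Primary outcome measure, success is absence of UI or a change of at least 3 points.

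**The concern.** A randomised comparison should rest on one model fixed before the outcome data are seen. Selecting terms by their fit to the outcome works against this in two ways.

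First, if the group term is itself a candidate, it survives only when it looks large enough. The estimate that is reported is then conditional on having passed a significance screen. Where the true effect is modest, that estimate may be missing from the final model or too large. Two analyses are described, and the text does not say which one gives the primary result.

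Second, the transformation rule tests the wrong quantity. ANCOVA and linear regression need well-behaved residuals, not a normally distributed baseline score. An entry threshold truncates T0 from below, so a normality test on T0 mainly detects the entry rule. If scores are transformed as a result, the treatment effect no longer lines up with the 3-point success criterion or with the planning differences, both of which are in points.

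**Working it through.** **Planned effects.** The article expects the average score "will lie at 8 and for MOTHERFIT2 at 9" and the 18-month mean "in the experimental group is 5". That gives differences of 8 − 5 = 3 (MOTHERFIT1) and 9 − 5 = 4 (MOTHERFIT2). The formula is n per arm = 2(1.960 + 1.282)² × SD² / difference², with two-sided alpha 0.05, 90% power and SD 5.

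- MOTHERFIT1: 2 × 10.51 × 25 / 9 = 58.4, so 59 (60 by the t-test version). Stated: 60. Then 60 / 0.8 = 75, as stated.
- MOTHERFIT2: 2 × 10.51 × 25 / 16 = 32.8, so 33 (34 by the t-test version). Stated: 35. Then 35 / 0.8 = 43.75, so 44. Stated: 45.

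The sample sizes therefore rest on differences of about 3 and 4 points with SD 5. The article also gives a care-as-usual mean of 10 for MOTHERFIT2. That would give a difference of 5 and 22 per arm, which does not match 35.

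**Simulated selection with the group term unprotected.** None of these assumptions is in the article except SD 5 and the evaluable numbers:

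- baseline-outcome correlation 0.5;
- four binary covariates with effects of 1 to 1.5 points;
- stepwise selection with entry at p < 0.05 and removal at p > 0.10, or backward elimination with removal at p > 0.10;
- a single end score in place of the linear trend;
- 1,000 trials per row.

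| Per arm | True effect | Group dropped: stepwise / backward | Mean when kept: stepwise / backward | Mean, fixed model |
|---|---|---|---|---|
| 60 | 3 | 3.5% / 1.9% | 3.09 / 3.06 | 3.02 |
| 35 | 4 | 4.2% / 1.7% | 4.14 / 4.08 | 4.04 |
| 60 | 1.5 | 57% / 44% | 2.23 / 2.06 | 1.47 |
| 35 | 1.5 | 71% / 59% | 2.71 / 2.50 | 1.50 |

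At the planned effects the excess is 2% to 4% (3.06/3 = 1.02; 4.14/4 = 1.035). At 1.5 points it runs from 2.06/1.5 = 1.37 to 2.71/1.5 = 1.81, that is 37% to 81%.

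**No true effect (3,000 trials).** Rejection rates were 0.053 (stepwise) and 0.058 (backward) against 0.051 for the fixed model at 60 per arm. At 35 per arm they were 0.051 and 0.058 against 0.048. The simulation standard error is √(0.05 × 0.95 / 3000) = 0.004, so the inflation is slight. With group and T0 forced in and only the other covariates selected, the rate was 0.057 at both sizes. The group effect was then always reported and unbiased (3.02 for a true 3; 1.48 for a true 1.5 at 60 per arm).

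**Transformation trigger.** Integer scores were drawn from a normal distribution with mean 8 or 9 and SD 5, restricted to 4-21 by the entry rule and the top of the scale. They failed Shapiro-Wilk at 0.05 in 100% of samples at n = 150 and 91% at n = 90. Three other assumed shapes on the same range gave 100% at n = 150 and 95-100% at n = 90.

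**Effect on scale.** No transformation is named, so take a logarithm as an illustration. A 3-point fall from 4 to 1 is a ratio of 0.25, and from 19 to 16 it is 0.84. The same clinical change in points becomes very different effects. A continent woman scores 0, which has no logarithm.

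**The case against.** The strongest reply is that the text can be read more kindly. The sentence listing the regression terms sets T0 and the group dummy apart from the other possible confounders, so selection may be meant for the confounders only. Forced terms and thresholds are also details that an analysis plan not shown here could settle. This stands as a possible reading. However, the selection sentence follows without an exemption, so the removal of the group term is permitted rather than stated.

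A reader might infer that if the group term is eliminated the trial has no treatment estimate. The article does not support that, because the preceding ANCOVA gives a group effect whatever selection does. What is missing is which analysis is primary.

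A reader might also infer that the p-values become badly wrong, or that selection does special damage. Neither follows. Type I inflation is slight, and the exaggeration is largely a significance filter. The fixed model, quoted only when p < 0.05, averages 2.22 and 2.73 at a true effect of 1.5 (60 and 35 per arm), much like the selected model. The protocol does not plan for an effect that small.

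The BMI and age cut-points may look data-driven, but they are written down in advance and only lose some information.

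On transformation, several points hold. It is only to be attempted. T0 is collected before randomisation, so treatment cannot steer the trigger. T0 also enters the linear trend, so it is not only a covariate. The plan does check residuals, outliers and normality of the trend. A transformed scale is not meaningless, and the 3-point responder definition survives on the raw scores. None of this makes normality of T0 the right condition.

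**Conclusion.** The point holds in a limited form. The article lets outcome-based selection settle the final regression for the main hypothesis without protecting group and T0, and leaves open which of two analyses is primary. If the group term is a candidate, the harm is small at the planned differences of 3 and 4 points and substantial if the true effect is about 1.5 points. These sizes depend on the assumed correlation, covariate effects and selection thresholds, and on using an end score instead of the trend. Confidence-interval coverage was not computed.

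The transformation rule is a separate fault. It is keyed to a property that the model does not need and that the entry criterion nearly guarantees will fail. This assumes that the Shapiro-Wilk test named for descriptive work is also the test behind the trigger. The consequence is an effect that may be on a scale mismatched to the success criterion and to the sample-size assumptions. Both faults are stated rules rather than omitted detail, and both should be corrected before analysis.

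**What to change.** - Name one primary model. One example is the ANCOVA of ICIQ-UI-SF in points at 18 months post-partum. This would replace the linear trend as the deciding analysis, so it is a choice to make openly. If the trend is kept as primary, the rules below apply to it unchanged.
- Retain group, T0 score, parity, BMI, age, pelvic-floor contraction ability and location (the level at which blocks are randomised) whatever their p-values.
- Delete forward/backward selection, or confine it to an analysis labelled exploratory. Label interactions with arm exploratory too.
- Delete the transformation trigger at T0. Keep points as the primary scale and handle non-normal residuals with robust or bootstrap standard errors.
- Optionally enter BMI and age as continuous variables, for a minor gain in precision.

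The sample size does not change. The cost is revised wording and a few degrees of freedom. In the simulations the fully fixed model held its type I error (0.051 at 60 per arm, 0.048 at 35) and always reported the group effect.

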Statistical analysis on the secondary outcomes of the study, such as the IIQ-7, the GPE and the EQ-5D-5 L will be handled in the same way as the primary outcome measure ICIQ-UI-SF. Process and structure indicators will be analysed with descriptive statistics and presented quantitatively as numbers and absolute and proportion data.

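### Interactions are selected for testing by main-effect significance in a stepwise model, a poor gate for effect modification that costs power to detect real modifiers of the motherfit effect

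*Protocol article*

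**What the plan says.** In the protocol article, Statistical methods, Analysis of main hypotheses, the dependent variable of the regression is each participant's linear trend in ICIQ-UI-SF. The candidate terms are described as follows: "Next to the baseline covariate measurement and the randomisation groups’ dummy variable, other possible confounding variables will be used". The named covariates are "Body Mass Index (BMI) before pregnancy (> 25), parity, maternal age (> 35 years) and the ability to perform a PFM contraction at baseline". The model is then chosen from the data: "Forward selection and backward elimination techniques will be used to determine the best fit of the data to a final regression model".

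The interaction rule follows: "Testing of interactive relationships between statistically significant effects of predictors in the final model will be done". A closing clause gives the treatment factor priority: "especially if it concerns the experimental between-randomisation groups’ factor". The rule covers interactions among any significant predictors, with those involving randomised group singled out. With baseline score and four covariates there are at most five group interactions.

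The only stated test level is general, under Descriptive analysis: "value < 0.05 will be considered to be statistically significant". Secondary outcomes (IIQ-7, GPE, EQ-5D-5L) "will be handled in the same way as the primary outcome measure ICIQ-UI-SF", so the rule carries over to them in both trials.

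**The concern.** A main effect answers whether outcomes differ, on average over both arms, between women with and without a characteristic. Effect modification asks whether the motherfit-CAU difference varies with that characteristic. Using the first question to decide whether the second is asked has two consequences. Which subgroups are examined depends partly on chance in the same data. A modifier must also pass at least two significance tests, or three if the group term must be significant too, before it can be reported.

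Ability to contract the pelvic floor shows what is at stake. It is checked at recruitment, it determines who receives individual instruction before joining a group, and it is a named covariate. Whether benefit depends on it is a natural question, and under this rule it may go unasked.

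**Working it through.** **The plan's own figures.** The article states no operating characteristic for the interaction tests, so the sample size is what can be reproduced. With n per arm = 2 × SD² × (1.960 + 1.282)² / difference²:
- MOTHERFIT1: 2 × 25 × 10.51 / 9 = 58.4, so 59 (stated 60).
- MOTHERFIT2, with 9 against 5: 2 × 25 × 10.51 / 16 = 32.8, so 33 (stated 35).

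The stated 60 and 35 completers per arm are used below.

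**Assumptions not in the article.** Residual SD σ = 4.2 (equal to 5 × √(1 − 0.54²), a baseline correlation of about 0.54); a 50:50 binary covariate; selection at 0.05 by backward elimination; a single score as outcome instead of the linear trend; a 3-point group effect in both trials.

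**Why the gate costs power.** Let N be the total and g the interaction in points.
- SE of the interaction = 4σ/√N.
- SE of the covariate's average effect, and of the group effect = 2σ/√N.
- If the covariate matters only under motherfit, its average effect over both arms is g/2.

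The gate test and the interaction test then have the same expected z, g√N/(4σ). In a balanced design they are uncorrelated. Detection under the gate is therefore roughly power × power × power of the group term, with power ≈ Φ(z − critical value).

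*60 per arm, g = 3.* Interaction SE = 16.8/10.954 = 1.534; z = 1.956; power Φ(1.956 − 1.98) = 0.49. Group: 3/0.767 = 3.91; Φ(1.93) = 0.973. Gated: 0.49 × 0.49 × 0.973 = 0.23. Simulation: 22% gated, 47% direct.

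*35 per arm, g = 3.* SE = 16.8/8.367 = 2.008; z = 1.494; power Φ(1.494 − 2.00) = 0.306. Group: 3/1.004 = 2.99; Φ(0.99) = 0.84. Gated: 0.306² × 0.84 = 0.08. Simulation: 8% gated, 28% direct. With the 4-point difference that reproduces the MOTHERFIT2 sample size, group power is Φ(3.98 − 2.00) = 0.976 and the gated figure is 0.09.

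*60 per arm, g = 6.* z = 3.91; power 0.973; gated 0.973³ = 0.92. Simulations: 87% to 90% gated, 96% to 97% direct. The formula runs slightly high because it ignores the residual variance added by the omitted interaction.

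| Interaction, acting only under motherfit | 60 per arm: gated / direct | 35 per arm: gated / direct |
|---|---|---|
| 3 points | 22% / 47% | 8% / 28% |
| 4 points | 49% / 71% | 19% / 49% |
| 6 points | about 90% / 97% | 49% / 79% |

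**Range over the residual SD** (60 per arm, g = 3, same formula), using the two SDs the article mentions:
- SD 5: z = 3/1.826 = 1.643, power 0.37; group 3/0.913 = 3.29, power 0.90; gated 0.37² × 0.90 = 0.12, against 0.37 direct.
- SD 3: z = 3/1.095 = 2.74, power 0.78; group power about 1; gated 0.78² = 0.61, against 0.78 direct.

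**Extreme case.** If the covariate shifts the score 3 points one way under CAU and 3 points the other way under motherfit, its average effect is zero. It passes the gate only by chance. Simulation: tested in 4.4% of trials, detected in 4.1%, against 97% directly.

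**False positives, a separate question.** With k independent tests at 0.05 the chance of at least one false group interaction is 1 − 0.95^k: 18.5% for k = 4 and 22.6% for k = 5. Correlation of 0.5 between five tests gives 18%. With the selection step simulated, the rate is about 1% when no covariate matters, about 6% if only baseline does, and 8% to 16% with covariate effects of 0.4 SD (N from 90 to 150).

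**The case against.** The strongest reply is that a main effect is not uninformative. Under 1:1 allocation a covariate that acts only under motherfit produces an average effect of half the interaction, so large modifiers usually pass the gate. That is right, and it is why the 6-point loss at 60 per arm is small. It does not help with moderate modifiers or with the smaller trial. The clause singling out the randomised factor might also be read loosely, as not requiring the group term to be significant. That changes little: the 3-point figure at 60 per arm becomes 0.49² = 0.24.

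A reader might draw four stronger conclusions that the article does not support.
- *That the rule produces false subgroup findings in about 21% of trials.* That rate needs all four covariates to have effects of 3 points, as large as motherfit itself. It comes from several unadjusted tests, and the gate reduces their number.
- *That modifiers without a main effect are never tested.* About 4% to 5% get through by chance. The economic evaluation also plans subgroups by age category and adherence, though these do not repair the clinical analysis.
- *That 4% against 97% is the typical loss.* It needs the crossover pattern.
- *That the absence of a multiplicity correction or exploratory label is itself an error.* Either could stand in the full protocol or an analysis plan not shown, and the 0.05 level is inferred from a general sentence.

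It is also fair to say that the ANCOVA comes first in the section, and nothing states that an interaction would replace the main conclusion.

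**Conclusion.** The point stands in limited form. The article states a positive rule for choosing interactions, so this is more than missing detail, and the rule selects on the wrong quantity. For a plausible modifier acting only under motherfit, with a 3-point interaction, it cuts detection to about half at 60 per arm (22% against 47%) and to under a third at 35 per arm (8% against 28%). The loss is slight for a 6-point interaction at 60 per arm and near total only in the crossover case.

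These sizes rest on the assumed residual SD, the even covariate split, the 0.05 selection level and the single-score outcome. The residual SD alone moves the 3-point result at 60 per arm between about 12% against 37% and 61% against 78%. The direction does not depend on it. False group interactions at an inferred unadjusted 0.05 occur in roughly 1% to 16% of trials in realistic scenarios, with a ceiling of about 18% to 23%; the gate does not cause this. The issue affects the secondary question of who benefits, not the primary comparison, and is a cheap improvement.

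**What to change.** Replace the interaction sentence in Analysis of main hypotheses with wording such as: The interactions of randomised group with [a short list fixed before the data are seen, drawn from baseline ICIQ-UI-SF and the four named covariates, for example ability to perform a PFM contraction] will each be tested whatever the significance of any main effect. They will be reported as estimates with 95% confidence intervals and interpreted as exploratory. The primary conclusion rests on the model without interactions.

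Apply the same wording to the secondary outcomes. The list should stay short, because testing all five at 0.05 would reach the 18% to 23% ceiling; the exploratory reading is what makes an unadjusted level acceptable.

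The cost is a wording change, with no extra participants or data. The sponsor must commit to the list in advance, and interaction results cannot be presented as confirmatory. Power for a 3-point interaction stays modest even when tested directly (47% and 28%), so a non-significant result should not be read as showing no modification.

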### Economic evaluation

#### General considerations

For both subgroups in MOTHERFIT1 and MOTHERFIT2, separate trial-based economic evaluations (EE) will be performed, but both EEs will have the same characteristics, except for the time horizon. The EE will take a societal and health care perspective, comparing motherfit group therapy with CAU. The time horizon for MOTHERFIT1 will be (about) 24 months starting from 12 weeks’ gestation (study inclusion) up to 18 months post-partum and for MOTHERFIT2 from approximately 6 weeks to 18 months post-partum. Cost-effectiveness ratios will be expressed as the societal cost per quality-adjusted life-year (QALY) (societal perspective), and the (health care) cost per woman, in whom UI is clinically relevant, reduced (primary outcome; health care perspective). Bootstrap analysis and cost-effectiveness acceptability curves will be constructed, showing for a range of threshold values the probability that motherfit group therapy is cost-effective. Sensitivity analyses and subgroup analyses (e.g. on age categories, adherent versus non-adherent women) will be performed to test for the robustness of the results.

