### Detailed study plan

#### Patient recruitment/consent procedure

The obstetrician/gynaecologist or midwife (case manager) at each centre will be responsible for identifying eligible participants. All women will receive written and digital (www.motherfit.net) general information about the motherfit study at:the first visit to the case manager and may be recruited from the second visit at 12 weeks or later until 27 weeks’ gestation (MOTHERFIT1)routine control at 6 weeks post-partum (MOTHERFIT2)

In case a woman is interested to participate, a simple vaginal examination is performed to check the ability to contract the pelvic floor muscles (Figs. 1 and 2). The woman will receive an envelope containing: patient information, two informed consent forms with return envelope and an information booklet on the medical scientific research of the Dutch Government [28]. The case manager fills in the name, telephone number and email address of the woman at a secure site (digital database), which can only be accessed by the researcher. After 1 week, the researcher will contact the woman by telephone and ask whether she has any questions regarding the study after reading the patient information. If the woman is willing to participate, she will be asked to fill in the two informed consent forms and return them to the researcher. The researcher will sign the two informed consent forms and return one to the participant.

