### Data collection and outcome measures

All data (electronic case report forms and questionnaires at baseline and follow-up) of the participants and case managers will be collected in a (web-based) digital central database. Demographic variables and personal characteristics will be registered by the Nederlandse Vereniging voor Obstetrie & Gynaecologie vragenlijst (NVOG-q) at baseline for MOTHERFIT1 and MOTHERFIT2.

MOTHERFIT1: data will be collected at baseline, 34 weeks of gestation, 6 weeks and 6 and 18 months post-partum.

MOTHERFIT2: data will be collected at baseline and 4, 9 and 18 months post-partum.

The case manager fills in a first survey after the inclusion of a participant. For MOTHERFIT1 these questions include, among others, expected delivery date and current medication use. Two weeks after delivery, case managers receive a second survey regarding delivery variables. For MOTHERFIT2 the case manager fills in identical surveys, except the question on expected delivery date.

Participants in the intervention group fill in a training diary and three questions regarding their general physical activity level, weekly. The PPTs will register attendance of the participant during the intervention period and send it by postal mail to the researcher.

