### Cost-analysis

The cost-analysis will be performed from both a societal and health care perspective. Resource use will be measured in natural units and will be valued in monetary terms by multiplying these units by the costs per unit. If available, standardised, national cost prices (e.g. specified by the recently updated Dutch guideline for cost research in health care will be used [46]. Costs are distinguished into motherfit programme costs including the group sessions and home-based part and costs of the mApp (initial and replacement costs for ICT hardware and software), health care costs (e.g. use of incontinence materials, visits to the general practitioner, gynaecologist, midwifery costs, visits to the PPT, surgery, etc.), non-health care costs (e.g. travel costs and productivity losses) and patient and family costs (time spent on the programme, informal care costs). Data on (health care) resource utilisation associated with SUI will be prospectively recorded during the study by the participants. Other health care, non-health care and patient and family costs will be collected by means of a standardised cost questionnaire to be filled out by patients. Costs occurring 12 months after study inclusion will be discounted at 4% according to the Dutch guidelines for economic evaluations health care [47].

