### Patient outcome analysis

The outcome for the cost-utility analysis (societal perspective) is defined in terms of QALYs from inclusion up to 18 months post-partum. The number of QALYs is derived from the adjustment of survival data with HRQL. HRQL will be measured with the EuroQol-5D (EQ-5D) instrument, which provides a descriptive health profile and a Dutch valuation set for obtaining utility scores from the EQ-5D [45]. The outcome for the cost-effectiveness analysis (health care perspective) is based on the proportion of women with clinically relevant reduction in UI at 18 months post-partum. Outcomes occurring 12 months following study inclusion will be discounted at 1.5% according to the Dutch guidelines for economic evaluations of health care [47].

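### MOTHERFIT1 economic evaluation: the stated horizon of about 24 months fits only early entrants; under the recruitment window it runs from about 21 to 24 months, which adds modest avoidable variance to incremental QALYs

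*Protocol article*

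**What the plan says.** The General considerations of the Economic evaluation fix one horizon for MOTHERFIT1: "The time horizon for MOTHERFIT1 will be (about) 24 months starting from 12 weeks’ gestation (study inclusion) up to 18 months post-partum". This treats inclusion and 12 weeks' gestation as the same moment.

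The Patient recruitment/consent procedure says that women "may be recruited from the second visit at 12 weeks or later until 27 weeks’ gestation (MOTHERFIT1"). Inclusion comes somewhat later than the first approach: "After 1 week, the researcher will contact the woman by telephone". Signed consent and the electronic baseline questionnaires then follow before randomisation (Allocation of participants).

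The accrual rules use the individual entry date. Under Patient outcome analysis, the cost-utility outcome "is defined in terms of QALYs from inclusion up to 18 months post-partum". Both discounting rules start from the same point: "Costs occurring 12 months after study inclusion will be discounted at 4" per cent (Cost-analysis) and "Outcomes occurring 12 months following study inclusion will be discounted at 1.5" per cent (Patient outcome analysis).

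The case manager's first survey, completed after a participant is included, records what is needed to derive gestational age at entry: "For MOTHERFIT1 these questions include, among others, expected delivery date and current medication use" (Data collection and outcome measures).

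**The concern.** Each woman's clock starts at her own inclusion and stops at a date fixed by her delivery. A QALY total is utility multiplied by time, so a woman who enters early collects more QALYs than one who enters late, whatever either treatment does. The same holds for any cost that accrues with time. The horizon sentence takes the earliest possible start and gives it as everyone's.

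Two things are at stake. A reader of the economic results would take every MOTHERFIT1 participant to contribute about 24 months, when the plan allows about 21. In addition, variation in entry date passes into the incremental QALYs, and from there into the bootstrap and the acceptability curves. Cost-effectiveness is the trial's secondary objective. Randomisation is in blocks of four by location, and gestational age at entry is not a named factor, so the arms can differ on it by chance.

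**Working it through.** **Inputs from the document.** Recruitment window 12 to 27 weeks' gestation; end of accrual 18 months post-partum; 75 women per arm (60 after the planned 20% dropout); discounting from 12 months after inclusion.

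**Assumptions, not in the document.** Birth at 40 weeks (range 37 to 42); mean utility 0.85; between-woman utility SD 0.10 to 0.20; entry uniform over 12–27 weeks, or over 12–20 weeks as an early-entry alternative; utility independent of accrual time. Conversions: 4.348 weeks per month, 52.18 weeks per year, 18 months = 78.27 weeks.

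**Step 1. Reproduce the stated horizon.** Months = (40 − entry week)/4.348 + 18. Entry at 12 weeks gives 28/4.348 + 18 = 24.4 months (23.8 to 24.9 for birth at 37 to 42 weeks). This matches the stated figure.

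**Step 2. The rest of the window.**

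| Entry (weeks) | Accrual (weeks) | Accrual (months) |
|---|---|---|
| 12 | 106.27 | 24.4 |
| 16 | 102.27 | 23.5 |
| 19.5 | 98.77 | 22.7 |
| 27 | 91.27 | 21.0 |

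For entry at 27 weeks the range is 20.3 to 21.5 months for birth at 37 to 42 weeks. The spread is 15 weeks, that is 3.45 months or 0.29 years. At utility 0.85 the earliest and latest entrants differ by 0.85 × 15/52.18 = 0.244 QALY; discounting at 1.5% changes this only to 0.241. The point at which discounting starts moves too, from 12 − 28/4.348 = 5.6 months post-partum (entry at 12 weeks) to 12 − 13/4.348 = 9.0 months (entry at 27 weeks).

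**Step 3. Chance difference between arms from entry date alone.** 95% range = 1.96 × SD(entry) × √(2/n) × 0.85/52.18.

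- Entry over 12–27 weeks: SD = 15/√12 = 4.33 weeks. With n = 75, 1.96 × 4.33 × √(2/75) = 1.39 weeks, or ±0.023 QALY. With n = 60 it is about ±0.025.
- Entry over 12–20 weeks: SD = 8/√12 = 2.31 weeks. With n = 75, 0.74 weeks, or ±0.012 QALY.

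**Step 4. Effect on the standard error of incremental QALYs.** With utility SD s, and accrual time with mean m and SD d in years, the QALY variance is s²m² + 0.85²d² + s²d². Adjusting for entry gestation removes the middle term.

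| Entry | m | d | s | SD unadjusted | SD adjusted | Ratio |
|---|---|---|---|---|---|---|
| 12–27 | 1.893 | 0.0830 | 0.10 | 0.2022 | 0.1895 | 1.067 |
| 12–27 | 1.893 | 0.0830 | 0.20 | 0.3854 | 0.3789 | 1.017 |
| 12–20 | 1.960 | 0.0443 | 0.10 | 0.1996 | 0.1960 | 1.018 |
| 12–20 | 1.960 | 0.0443 | 0.20 | 0.3939 | 0.3921 | 1.005 |

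For entry over 12–27 weeks with 75 per arm, the 95% half-width (1.96 × SD × √(2/75)) is 0.065 unadjusted against 0.061 adjusted at s = 0.10, and 0.123 against 0.121 at s = 0.20.

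**Step 5. Allowing for the lost degree of freedom.** A simulation of 20,000 trials with 75 per arm compared the plain difference with a regression on arm and entry gestation. The SE ratios, in the order of the table, were 1.065, 1.017, 1.014 and 1.002. Steps 4 and 5 together give about 0.2% to 7%.

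**The case against.** The case against is strong on importance.

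- **No bias.** Gestational age at entry is settled before allocation. A reader might infer that incremental QALYs are distorted or that the bootstrap intervals are invalid. Neither follows: randomisation balances entry time in expectation, and the bootstrap captures its variation. This stands in full.
- **The operative rule is right.** An analyst who follows Patient outcome analysis would compute each woman's accrual correctly. A reader might infer that everyone will be credited with 24 months; the document does not say so. Only the horizon sentence is wrong. Its hedge covers 24.4 or 23.5 months but not 21.
- **Adjustment is detail for a fuller document.** A journal article may leave covariate adjustment of QALYs to the full protocol or analysis plan, and nothing here rules it out. So its absence is not an error. The adjustment is offered as an improvement alongside a correction that the text does need.
- **The size rests on assumptions.** The 7% needs uniform entry and the smallest utility SD; at the other end the gain is close to nothing. The Background puts SUI prevalence at about 9% in the first trimester and 32% in the second, so uniform entry from 12 weeks is doubtful, but the document does not support early clustering either.
- **The one-week wait.** It might seem to narrow the window to 13–27 weeks. But if 27 weeks limits recruitment, inclusion can also slip to 28 weeks (20.8 months at birth at 40 weeks), so there is no basis for moving only one end.
- **Scope.** The health care perspective uses the proportion with clinically relevant reduction at 18 months post-partum, which does not accrue with time. The motherfit sessions are fixed at eight, so that cost does not grow with earlier entry. Both points stand.

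**Conclusion.** The concern holds in a limited form. The horizon sentence contradicts the recruitment window: assuming birth at 40 weeks, accrual is about 21 to 24 months rather than about 24 for all. The consequence is imprecision, not bias. Not adjusting inflates the SE of incremental QALYs by about 0.2% to 7%, given mean utility 0.85, utility SD 0.10 to 0.20, and uniform entry over 12–20 or 12–27 weeks. The effect on time-accruing costs is unquantified because the document gives no cost figures. There is no effect on the responder proportion used as the health care perspective outcome. Nothing shows that a cost-effectiveness conclusion would change.

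A reader might also infer that entry gestation belongs in the primary ICIQ-UI-SF model, since the candidate covariates there are "Body Mass Index (BMI) before pregnancy (> 25), parity, maternal age (> 35 years) and the ability to perform a PFM contraction at baseline" and do not include it. The document does not support that step: the ICIQ-UI-SF endpoint is timed from birth, its baseline score is already a covariate, and no gain has been shown. The point is optional and confined to the MOTHERFIT1 economic evaluation.

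**What to change.** 1. Restate the MOTHERFIT1 horizon in General considerations as about 21 to 24 months, from individual inclusion (recruitment at 12–27 weeks' gestation) to 18 months post-partum.
2. In the MOTHERFIT1 trial-based evaluation, estimate incremental QALYs and incremental costs adjusted for gestational age at inclusion, entered as a continuous variable, within each bootstrap replicate. Derive it from the expected delivery date, not the actual one, so that the covariate is not affected by anything after randomisation.

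The cost is one reworded sentence and one degree of freedom per model, with data already collected. Care, visits, recruitment and the ICIQ-UI-SF models stay as they are.
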